### Statistical analysis and methods

Distribution of subjects in the study will be presented as in the flowchart reported in Fig 4.

**Fig 4 pone.0283944.g004:**
[figure not shown]
Flowchart summarizing the distribution of subjects in the study. sPTB = spontaneous preterm birth.

The CSI is a continuous variable. Consecutive CSI values (CSI 1, CSI 2 CSI 3) will be analysed and/or pooled as mean value, single sequential values, max or min value of the sequence, or combination of those and other possibilities.

Descriptive statistical methods will be used to summarize the data from this study. Unless stated otherwise, the term “descriptive statistics” refers to number of subjects (n), mean, median, standard deviation (SD), minimum, and maximum for continuous data and frequencies and percentages for categorical data. Multi-variate linear and logistic regression analysis will be performed, correlations and predictive capabilities for the CSI alone and in combination with other collected data will be evaluated. The level of significance will be 0.05.

The investigator will actively ask for any Adverse Events (AEs) during the visits. At each clinical investigation visit the investigator will assess and record any AE in detail in the source data. The Investigator will evaluate Serious Adverse Events (SAEs) regarding causality and seriousness. The number and percentage of participants with SAEs will be displayed by body system and preferred term using Medical Dictionary for Regulatory Activities (MedDRA) version 22.0 or higher, by cohort group and overall. Summaries in terms of severity and relationship will also be provided.

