#### Sample size calculation

In this pilot study, up to 142 subjects will be enrolled to have a total of 120 subjects (estimated dropout rate of 15%) for the study; pessary cohort: 60 (up to 71 recruited), non-pessary cohort: 60 (up to 71 recruited). Currently, it is difficult to perform a formal power analysis since the Pregnolia System is a novel device and there exist only limited clinical data.

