### Study objectives

The primary objective is to determine the absolute value of CSI and its change over time in women undergoing pessary treatment, in comparison to normal pregnancies, when measured at 18^+0^ to 24^+6^ weeks and at the follow-up visit (4 weeks later).

The secondary objective is to determine the correlation of the initial CSI and CSI changes with birth outcome (gestational age at birth).

The safety objective is the safety of the device, by assessing incidence, severity, and seriousness of device-related adverse events.

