### Study endpoints

The primary endpoint of the study is the Cervical Stiffness Index (CSI, in mbar). The secondary endpoint is patient delivery data (including gestational age, mode of delivery and complications). The safety endpoint is device-related adverse events (incidence, severity, and seriousness).

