#### Assessment of primary endpoint

The primary endpoint is assessed via 3 consecutive CSI measurements with the Pregnolia System to obtain the CSI values. During all the visits the CSI measurements with the Pregnolia System are done according to the IFU. Briefly, the Pregnolia Control Unit is set up and one Pregnolia Probe, single use and sterile, is connected to the control unit. The woman is prepared for a speculum-based vaginal examination, excessive mucus is removed, and the measurement site is checked for contraindications / withdrawal criteria. The pump is started, and the probe is gently applied on the cervix at 12 o’clock position. The user is guided through the different steps of the measurement by audio signals. The CSI assessment is performed 3 consecutive times, and thereafter the probe is removed. The results (CSI1, CSI2 and CSI3) are reported in the CRF. The study team will be trained to ensure the right handling of the device.

The measurements should be made consecutively. In case of a measurement failure, this will be recorded in the CRF.

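### The form of the primary CSI endpoint is left open-ended while one 0.05 level applies; one summary and one leading contrast should be fixed before analysis

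*Protocol article*

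**What the plan says.** All references are to the protocol article.

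- **Study endpoints** names the primary endpoint only as the CSI in mbar, without a summary, visit or contrast.
- **Assessment of primary endpoint**: "The primary endpoint is assessed via 3 consecutive CSI measurements with the Pregnolia System to obtain the CSI values". CSI1, CSI2 and CSI3 go into the case report form. On failed readings it says: "In case of a measurement failure, this will be recorded in the CRF".
- **Study objectives**: "The primary objective is to determine the absolute value of CSI and its change over time in women undergoing pessary treatment", compared with normal pregnancies, at 18+0 to 24+6 weeks and four weeks later.
- **Statistical analysis and methods** gives the only rule that turns three readings into an endpoint. They will be "analysed and/or pooled as mean value, single sequential values, max or min value of the sequence, or combination of those and other possibilities". The section then plans descriptive summaries, linear and logistic regression, correlations and an evaluation of prediction, and adds: "The level of significance will be 0.05". No multiplicity control is stated.
- **Sample size calculation** calls the study a pilot with 60 completers per cohort. It gives no power: "Currently, it is difficult to perform a formal power analysis since the Pregnolia System is a novel device".
- **Discussion** puts forward the hypothesis of a significant CSI difference between the cohorts.

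**The concern.** The article is not merely silent here. It states a rule for the primary endpoint, and the rule sets no limit. Six forms can be counted from the wording (the mean, each of the three readings alone, the maximum, the minimum), followed by combinations and a remainder without bounds. None has priority. The primary objective joins two quantities, level and change, under one 0.05 level.

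At stake is what a significant cohort difference in CSI would mean. If the summary may be picked once the results are known, 0.05 is no longer the error rate of the reported finding, and a reader cannot tell whether the summary was chosen for its result. Not knowing the variance of a new device explains the missing power calculation. It does not explain the open endpoint, because choosing a summary needs no variance estimate.

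**Working it through.** **The plan's own figure.** 60 / (1 − 0.15) = 70.6, rounded up to 71 per cohort; 2 × 71 = 142. This reproduces the stated enrolment. The 60 itself cannot be derived, since no effect size or SD is given.

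**Inputs from the article.** 60 completers per cohort; three readings per visit; two visits; level 0.05; six named forms.

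**Assumptions, none of them in the article.** Two-sided t-tests; normal data; correlation r between readings at one visit from 0.5 to 0.95; correlation of the woman's underlying value between visits of 0.6 (0.5 also tried).

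**Upper bound.** Six independent tests would give 1 − 0.95^6 = 0.265. Readings on one cervix are correlated, so the true figure is lower and has to be simulated.

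**Simulation under no cohort difference** (10,000 runs per setting). Reading j of woman i is √r · s_i + √(1 − r) · e_ij, with s_i and e_ij standard normal. Each form is compared between the cohorts at baseline and for change. The table gives the chance of at least one p < 0.05, with between-visit correlation 0.6.

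| r | six forms, baseline | six forms, change | all twelve | mean only, both contrasts |
|---|---|---|---|---|
| 0.5 | 15.3% | 17.8% | 27.9% | 9.6% |
| 0.7 | 12.6% | 15.2% | 23.9% | 9.4% |
| 0.8 | 11.0% | 13.2% | 21.3% | 9.0% |
| 0.9 | 8.9% | 10.7% | 17.5% | 8.9% |
| 0.95 | 7.2% | 9.0% | 14.5% | 8.6% |

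With between-visit correlation 0.5, change runs from 17.4% down to 9.2% and all twelve from 27.2% to 14.7%. Allowing for differences between simulation runs, the ranges are about 7–16% for baseline and 9–18% for change. Combinations and unnamed forms are not counted and could only raise them.

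**Separating the two causes.** One form with one contrast gives 5% (4.7% to 5.5% in these runs). One form with two contrasts gives about 9%; two independent tests would give 1 − 0.95² = 9.75%. So the twelve-test column reflects partly the free summary and partly the two contrasts. Only the single-contrast columns measure the effect of the open summary alone.

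**After the fix.** The mean, with each contrast tested at 0.025, gives 4.2% to 5.2% overall.

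**The case against.** The strongest case on the other side has four parts.

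1. *The study is a non-interventional pilot.* It has no power calculation, a descriptive emphasis, and a primary objective worded as determining CSI values. The 0.05 sentence follows the one on regression and prediction, not the one on CSI forms. This stands as a reason for lower severity. It does not dispose of the point, because a significance level is set and a significant cohort difference is hypothesised.
2. *Nothing says that every form will be tested and the best one reported.* True. The percentages show what the wording allows, not what is planned. They also rest on assumed correlations, and three readings taken in one probe application may correlate highly, which points to the lower end.
3. *The full protocol or an analysis plan may settle the form.* It may. But the article states an open list rather than deferring to another document, and that statement needs replacing or a cross-reference.
4. *The mean is not dictated by the documents.* Correct; it is a reasonable choice, not the only one. What matters is that one is fixed.

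Two stronger readings are tempting and not supported. A reader might infer that the three readings will be stacked as if independent. The article does not say so, and single sequential values can equally mean one reading per woman, so no pseudo-replication can be charged. A reader might also infer that the maximum or minimum would bias the cohort comparison when readings fail. The expected maximum is +0.85 within-woman SD with three readings and +0.56 with two, but a bias between cohorts needs failures that are left unrepeated and differ by cohort. The article gives no failure rate and does not say whether a failed reading is repeated.

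**Conclusion.** The point holds, as something that should be fixed rather than a critical flaw. The article gives its primary endpoint an unlimited set of forms under one 0.05 level, with no form or contrast in the lead. If the six named forms were each tested and the best reported, the false-positive rate for one contrast would be roughly 7–16% at baseline or 9–18% for 4-week change. This assumes 60 per cohort, two-sided t-tests, reading correlation 0.5 to 0.95 and between-visit correlation 0.5 to 0.6. Testing both contrasts raises it further, to about 9% even with the mean alone.

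A reader might take the 26.5% for six independent tests, or the twelve-test column, as the cost of the open summary. Neither is: the first ignores the correlation between readings, and the second includes the effect of having two contrasts. Nor do the documents show that the baseline difference must be tested before the change. The abstract's stated aim is whether a pessary stabilises stiffness, and a rule testing change only after a significant baseline difference could leave that question untested.

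**What to change.** Replace the sentence on pooling with, for example:

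> The primary CSI value at a visit is the mean of the valid consecutive readings; single readings, maximum, minimum and other combinations are sensitivity or exploratory analyses without significance claims.

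The mean uses all readings, and its expected value does not shift with the number of valid ones.

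Then, before analysis, do one of two things: name one contrast (baseline difference or 4-week change) as primary, or split the 0.05 between the two. Which contrast leads is for the sponsor to decide. If an analysis plan already settles this, cite it and make the wording agree.

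**Cost.** One paragraph, with no additional women, visits or measurements. The study gives up the freedom to choose a summary afterwards. Splitting alpha also costs some power per contrast. As an illustration by normal approximation, a contrast with 80% power at 0.05 would have Φ(1.960 + 0.842 − 2.241) = Φ(0.561) ≈ 71% at 0.025. Naming one primary contrast avoids that loss for the contrast named.

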#### Monitoring

Monitoring at the investigator’s site during the study will be carried out to follow up the progress of the clinical investigation, to assure outmost accuracy of the data and to detect possible errors as early as possible. A Monitoring plan (according to ISO 14155 as far as applicable) pre-defines the amount of monitoring.

## Discussion

The study aims to evaluate whether patients indicated for pessary treatment have *a priori* a lower ectocervical stiffness than normal pregnancies. Moreover, this study aims to evaluate the impact of treatment with pessary on measured ectocervical stiffness, and whether it, or its changes correlate with birth outcome.

The uterine cervix plays a fundamental role in ensuring that a pregnancy is carried to term, while securing a closed uterus throughout gestation, it progressively softens, and finally opens to allow delivery. This constitutes a striking transformation of the tissue structure and characteristics, constituting a complex biomechanical process, part of a larger context of dynamic changes in structural forces, loads, deformations, and material and biochemical properties that occur during pregnancy. When a cervix is no longer structurally sound, it cannot perform its function adequately, which may lead to premature birth. Multiple aetiologies can lead to such a failure, but the overall knowledge of what in fact leads to cervical failure is far from complete.

The major parameter currently used to aid the identification of those women at risk of delivering preterm is the measurement of cervical length using transvaginal ultrasound. Cervical shortening is predictive of preterm birth, however cervical length has only limited predictive capacity [28, 29]. Understanding of cervical remodelling is fundamental for prediction of sPTB and to avoid pessary failure. The Pregnolia system is a device that performs a biomechanical function, being able to describe the biomechanical parameters of the cervix accurately and quantitatively.

With improved prediction of sPTB, asymptomatic women may benefit through early detection of lower or declining cervical stiffness values and receive pessary therapy even before cervical shortening [30].

This study investigates a fundamental biomechanical parameter of the cervix–likely connected to the competency of the cervix–in order to assess its contribution to an existing therapy. The benefit of this study could lead to better identification of patients that can or cannot benefit from the pessary therapy, and therefore lead to better preterm birth management.

Our study will lead to a better understanding of the impact of the use of pessary on ectocervical stiffness. We hypothesise that the CSI values may differ significantly across cohorts in the study. We are confident that the CSI in combination with TVUS, could be a potential diagnostic tool, which enables the identification of the group of pregnant women for the antenatal cervical pessary treatment.
